## Abstract

**Background:**

Psychoneurological symptom clusters (PNSCs) are common in patients with ovarian cancer and are associated with reduced quality of life, treatment interruption, and poor prognosis. However, effective interventions for PNSCs remain limited. Traditional Chinese medicine may provide comprehensive benefits for symptom management.

**Objective:**

This study aims to evaluate the efficacy and safety of the TiaoShenZhiAi (TSZA) regimen in alleviating PNSCs in patients with ovarian cancer and to assess its effects on quality of life and survival outcomes.

**Methods:**

A total of 316 patients with ovarian cancer aged 18 to 70 years with PNSCs will be included and randomly divided into 2 parallel groups. Both groups will receive standard treatment for ovarian cancer as the basic treatment. The intervention group will receive the TSZA regimen, that is, Compound Ciwujia Granules (containing *Acanthopanax senticosus* and *Schisandra chinensis*) combined with psychological intervention. The control group will receive a low-dose active control (simulated Compound Ciwujia Granules) combined with psychological intervention. The primary outcome is the remission rate of PNSCs at 3 months. The secondary outcome measures include the Pittsburgh Sleep Quality Index, the Patient Health Questionnaire-9, the Generalized Anxiety Disorder-7 scale, the revised Piper Fatigue Scale, the European Organization for Research and Treatment of Cancer Quality of Life Questionnaire - Core 30 Quality of Life Scale, the traditional Chinese medicine syndrome scale, sleep quality, sleep diary, and the 1-year survival analysis. In addition, this study also includes a series of exploratory indicators (including functional magnetic resonance imaging, biomarkers of peripheral blood and tumor tissue, proportion of immune cells, cytokine levels, hypothalamic-pituitary-adrenal axis function, and immune gene expression analysis) and safety indicators (including vital signs, liver and kidney function, and electrocardiogram). The study outcomes will be evaluated based on different indicators during the treatment period (baseline and the 1st, 2nd, and 3rd mo of enrollment) and the follow-up period (the 6th, 9th, and 12th mo of enrollment). Data analysis will be conducted using R (version 4.5.3) software. A one-sided *P* value of <.03 will be considered statistically significant.

**Results:**

This study is designed to enroll a total of 316 participants. Participant enrollment is set to commence in October 2025, with no recruitment having occurred as of April 2026. The recruitment period will extend until September 2028 or until the target enrollment is met. Data analysis is scheduled for November 2028, with submission of the trial results to a peer-reviewed journal anticipated by May 2029.

**Conclusions:**

This study will evaluate the efficacy of the TSZA regimen in managing PNSCs in patients with ovarian cancer and generate clinical evidence for a new therapeutic option that improves quality of life and alleviates the symptom burden.

## Introduction

### Background

Malignant tumors represent a major global public health challenge. According to the latest World Health Organization (WHO) statistics, cancer is the second leading cause of death worldwide. The global burden of cancer continues to rise [1], with gynecological malignancies—such as ovarian cancer and cervical cancer—constituting a substantial proportion of cancer-related incidence and mortality among women. Although current comprehensive treatment strategies have significantly improved patient survival, multiple symptoms resulting from both the disease and antitumor therapies continue to severely affect patients’ quality of life, treatment compliance, and long-term prognosis [2,3].

Since the initial description of symptom co-occurrence in patients with cancer [4], the concept has evolved into the “symptom cluster,” defined as a stable group of 2 or more interrelated symptoms that often share underlying mechanisms and result in clinical outcomes more severe than the sum of individual symptoms [5-9]. Despite the lack of a singular consensus on its definition, it is widely recognized that symptom clusters are complex and heterogeneous. Their presence is strongly associated with diminished quality of life, increased risk of treatment interruption, and poorer prognosis, necessitating a shift from single-symptom management to a more holistic, cluster-based intervention approach.

Currently, intervention strategies for symptom clusters primarily fall into 2 categories: pharmacological and nonpharmacological treatments. Pharmacological management follows the principle of symptomatic support, wherein specific medications are selected based on the patient’s predominant symptoms—for instance, analgesics for pain relief or anxiolytic and antidepressant agents for alleviating anxiety and depression. Nonpharmacological interventions include a variety of approaches such as structured exercise, mindfulness meditation, professional psychological support, and music therapy, among others [10-12]. Although these interventions have become integral to comprehensive symptom management, they tend to emphasize general applicability and have yet to evolve into systematic protocols tailored to specific cancer types. This lack of personalized and structured approaches may limit further improvement in therapeutic outcomes.

Surgery remains the cornerstone of treatment for ovarian cancer. However, bilateral oophorectomy induces a precipitous decline in estrogen levels, leading to a constellation of sequelae, such as premature menopausal symptoms, sexual dysfunction, and altered body image [13,14]. The loss of reproductive organs can profoundly affect a woman’s self-identity, body perception, and gender identity [15], often resulting in significant psychological distress [16]. This internal conflict is frequently exacerbated by a discrepancy between societal stereotypes of femininity and the patients’ lived experiences, which can contribute to social withdrawal and strained family relationships [17].

Furthermore, the clinical prognosis adds another layer of complexity. Approximately 80% of patients with ovarian cancer are diagnosed at an advanced stage, with approximately 75% experiencing disease recurrence within 2 years. The 5-year overall survival (OS) rate for advanced-stage disease remains dismally low, ranging from 10% to 40% [18]. This stark clinical reality imposes a substantial psychological burden on patients. Compounding this are therapeutic challenges—including platinum resistance, limited targetable mutations in homologous recombination repair pathways, and an immunologically inert tumor microenvironment—which further intensify psychological distress in patients from a prognostic standpoint [19].

In summary, the interplay of surgical, psychological, social, and prognostic factors creates a complex web of stressors that collectively contribute to the high prevalence of psychoneurological symptom clusters (PNSCs) in patients with ovarian cancer.

Traditional Chinese medicine (TCM) emphasizes holistic regulation, with accumulating evidence demonstrating its efficacy in managing cancer-related symptom clusters. For instance, acupuncture significantly alleviates chemotherapy-induced nausea and vomiting [20] while also improving clusters comprising pain, fatigue, and sleep disturbances [21]. Furthermore, TCM interventions effectively relieve menopausal-like symptoms—such as hot flashes and insomnia—arising from treatment-induced endocrine deficiencies [22]. Mind-body exercises such as Tai Chi have even exhibited therapeutic effects comparable to cognitive behavioral therapy (CBT) for insomnia [23].

Building on these foundations, together with insights from our team’s clinical experience and preliminary small-scale studies, we have developed an integrative interventional protocol named the “TiaoShenZhiAi” (TSZA) regimen. Rooted in the TCM philosophy of “Regulating the Spirit to Treat Cancer,” the TSZA regimen is designed as an interdisciplinary oncological approach targeting psychoneurological symptoms associated with cancer, with the aim of improving patient survival and quality of life. In this study, the TSZA regimen specifically refers to a combination of standard-dose Compound Ciwujia Granules and a structured psychological intervention.

We have initiated this multicenter randomized controlled trial to rigorously evaluate the efficacy of the TSZA regimen in patients with ovarian cancer and PNSCs. Beyond clinical symptom remission, this study aims to enhance treatment adherence and potentially extend survival. Crucially, by integrating multimodal neuroimaging (functional magnetic resonance imaging [fMRI]) and targeted proteomics, we seek to elucidate the underlying biological signatures of PNSCs and the restorative mechanisms of the TSZA regimen, thereby advancing precision intervention strategies in integrative oncology.

### Objectives

The primary objective of this study is to evaluate the efficacy and safety of the TSZA regimen in alleviating PNSCs among patients with ovarian cancer. The secondary objectives include assessing its impact on patients’ quality of life and survival outcomes. Furthermore, the study aims to explore the characteristics of the patient population that derives benefit from the TSZA regimen for these symptoms.

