### Interventions

In this trial, both the intervention and control groups will receive standard-of-care treatment for ovarian cancer as the foundational therapy, in accordance with the 2024 NCCN International Guidelines. This may include platinum-based chemotherapy and/or targeted, antiangiogenic, or hormonal agents, as clinically indicated.

Both the intervention and control groups will receive the same psychological intervention. The intervention is based on CBT and mindfulness theory and is adaptively designed to address the characteristics of the PNSC in patients with ovarian cancer. It comprises a total of 12 sessions. The intervention is delivered in an online prerecorded format, once weekly, with each session lasting approximately 30 to 45 minutes. The materials are distributed to participants on schedule by the investigators according to a treatment manual. The session content includes cognitive restructuring of illness perceptions, pain tolerance, understanding and expressing interpersonal needs, family and social support, comorbidity of depression and sleep disturbances, sleep hygiene education, the theoretical basis of insomnia, stimulus control, cognitive restructuring for insomnia, emphasis on long-term coexistence, finding meaning within limitations, and relapse prevention. All sessions will be recorded by qualified mental health professionals from the Shanghai Mental Health Center, China. Prior to release, each session script is independently reviewed by another psychotherapist or the principal investigator to ensure objectivity, avoid leading statements or overpromising, and comply with ethical requirements for psychooncological interventions. To ensure consistency of intervention delivery across centers, standardized prerecorded materials are used at all sites. Investigators at each center receive unified training prior to study initiation, and intervention adherence is centrally monitored and recorded by the study team.

In addition, participants in the intervention group will receive the TSZA regimen, which consists of Compound Ciwujia Granules (containing *Acanthopanax senticosus* and *Schisandra chinensis*) combined with psychological intervention. The granules will be administered twice daily, one sachet each time, 30 to 60 minutes after meals, for a continuous period of 3 months.

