The control group will receive matching low-dose active control granules (containing 10% of the active ingredients found in Compound Ciwujia Granules), which are identical in appearance, odor, and taste to the investigational drug, following the same dosing schedule.

During the study period, the use of any medications not specified in the study protocol is prohibited. In principle, participants should not take other Chinese herbal medicines, Chinese patent drugs with sedative or sleep-promoting claims, biologics, or any other agents that may potentially affect sleep, fatigue, or mental health. Any use must be reported.

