### Outcomes

#### Primary Outcome

The PNSC score is constructed based on the 4 most relevant symptoms (fatigue, sleep disturbance, distress, and sadness) from the MDASI-OC scale, in accordance with its usage guidelines [24]. Each symptom is rated on an 11-point scale, ranging from 0 (“no symptom”) to 10 (“the most severe imaginable”). The primary efficacy end point of this study is the difference in the PNSC remission rates between the intervention and control groups at 3 months after enrollment. Given that there is no universally accepted evaluation standard for the remission of this specific cluster, “remission” is defined in this protocol through expert consensus. A participant is classified as in “remission” if they meet at least one of the following PNSC-specific criteria: a ≥50% reduction in the total PNSC score relative to the baseline or an absolute PNSC score falling below the threshold of 4 after the intervention. While the primary comparison between the 2 groups will focus on the 3-month mark, longitudinal assessments will be conducted at baseline and at 1, 2, 3, 6, 9, and 12 months after enrollment to monitor symptom dynamics.

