## Discussion

This study is a multicenter, randomized, double-blind clinical trial with a low-dose positive control, and it will enroll 316 patients with ovarian cancer and PNSCs. The aim is to test the effect of the TSZA regimen on the symptom cluster of fatigue, insomnia, anxiety, and depression. The study also follows survival and measures inflammatory factors, immune function, neuroimaging, and multiomics to confirm its clinical value and explore its biological mechanism.

As noted earlier, the high rate of PNSC in patients with ovarian cancer is not due to one factor but results from surgery, chemotherapy, psychological stress, lack of social support, and uncertain prognosis. These factors form a complex stress network and trigger a cascade of symptoms [35]. Studi

es show that chronic stress keeps the HPA axis active and disrupts secretion rhythms [36]. This long-term imbalance is a biological basis of PNSC, and it also reduces natural killer cell activity and increases proinflammatory cytokines, which creates an immune-suppressive environment that supports tumor growth and spread [37]. For example, basic research shows that chronic stress increases glucocorticoids and disrupts neutrophil circadian rhythm and promotes neutrophil extracellular traps, which helps build a premetastatic environment [38]. Clinical data also show that patients with anxiety or depression have shorter PFS [39]. This study focuses exactly on key points of the psychoneuroimmune axis.

The unique advantage of the TSZA regimen is that it combines herbal treatment with psychological intervention. The main components of Compound Ciwujia Granules, such as eleutheroside, have been shown to regulate the HPA axis and increase brain-derived neurotrophic factor, so they improve cognitive function and emotional stability at the molecular level [40-42]. In addition, a single intervention is not enough to deal with complex cancer-related symptom clusters. For symptom clusters with emotional and cognitive problems, the effect of drug treatment is often limited. Given that standard psychological interventions such as CBT have strong evidence in oncology [43], they are integrated into our protocol to optimize therapeutic outcomes. This approach uses cognitive adjustment to rebuild coping strategies and improve psychological resilience, and it works together with Compound Ciwujia Granules to form a combined internal and external treatment model.

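### The primary contrast tests full-dose against 10%-dose granules on a shared psychological programme, not the TSZA regimen named in the objective

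*Protocol article*

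**What the plan says.** The Background section of the protocol article states that "the TSZA regimen specifically refers to a combination of standard-dose Compound Ciwujia Granules and a structured psychological intervention". The Objectives section makes it the primary aim to "evaluate the efficacy and safety of the TSZA regimen in alleviating PNSCs among patients with ovarian cancer". The Abstract (Objective and Conclusions) and the opening of the Discussion frame the trial in the same way, as an evaluation of the regimen.

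The Interventions section then says: "Both the intervention and control groups will receive the same psychological intervention". The Abstract's Methods paragraph agrees: "The control group will receive a low-dose active control (simulated Compound Ciwujia Granules) combined with psychological intervention". The control granules are described in Interventions as "containing 10% of the active ingredients found in Compound Ciwujia Granules", taken on the same schedule, and the Blinding section gives the same 10% figure. Both arms also receive standard ovarian cancer treatment. The primary endpoint is "the difference in the PNSC remission rates between the intervention and control groups at 3 months after enrollment".

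The Discussion presents the pairing of herbal and psychological treatment as the regimen's distinctive strength and says of the psychological part that "it works together with Compound Ciwujia Granules to form a combined internal and external treatment model".

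**The concern.** The objective names a two-component regimen, but randomization separates the arms on one component only, the granule content. The psychological component is part of the thing to be evaluated and is also given in full to the comparator.

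Two misreadings are at stake. If the trial is positive, a granule-dose effect would be credited to the combination, including the claim that its parts work together. If the trial is null, it could be read as failure of the regimen even though both arms may have improved through the shared programme. The second risk is real on the protocol's own reasoning, because the Discussion says that psychological interventions such as cognitive behavioural therapy have strong evidence in oncology.

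**Working it through.** **1. What differs between the arms**

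| Element | Intervention | Control | Source |
|---|---|---|---|
| Standard cancer treatment | yes | yes | Interventions |
| Psychological programme, 12 sessions | yes | same | Interventions; Abstract, Methods |
| Granule content | 100% | 10% | Blinding; Interventions |
| Dosing schedule | same | same | Interventions |

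One sentence in Interventions says that the intervention group receives the TSZA regimen in addition, combined with psychological intervention. Taken alone, it could suggest extra sessions. The statement that both groups receive the same psychological intervention, and the Abstract, rule that out. Granule content is the only difference.

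**2. What the contrast estimates**

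Let p_F be 3-month remission with full-dose granules plus the programme, p_L with 10% granules plus the programme, and p_0 with standard care alone.

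- The trial estimates p_F − p_L.
- The effect of the whole regimen over standard care is p_F − p_0 = (p_F − p_L) + (p_L − p_0).

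No arm provides p_0, so the second term is not estimated. On an additive scale, with G the full-dose effect, g the 10%-dose effect and P the psychological effect, the arm difference is (G + P) − (g + P) = G − g, while the regimen effect is G + P. P cancels. Joint action would also need an arm with granules but without the programme, and there is none.

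**3. Direction**

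The gap between the two quantities is p_L − p_0, or P + g on the additive scale. If the programme and the low-dose granules together do no harm, the gap is zero or positive, so the trial's difference is no larger than the regimen effect. If p_F = p_L, the regimen effect equals p_L − p_0, which the trial leaves unknown.

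**4. Size on the plan's own figures**

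The Sample Size section assumes control remission of 10%, intervention remission of 40% and a superiority margin of 15 percentage points, with one-sided α 0.025 and power 0.80. Its figure reproduces with unpooled variance:

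n = (1.960 + 0.842)² × (0.10 × 0.90 + 0.40 × 0.60) / (0.30 − 0.15)² = 115.1, rounded up to 116 per group; 116 / 0.8 = 145 after dropout.

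The 10% belongs to a control arm that already receives the programme and the low-dose granules, so p_L = 0.10. The protocol does not give p_0. If neither component is harmful, p_0 lies between 0 and 0.10:

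- p_0 = 0.10: regimen effect 40 − 10 = 30 points, gap 0.
- p_0 = 0: regimen effect 40 − 0 = 40 points, gap 10.

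The trial's planned difference is 30 points in both cases. The sample size is built on the arms as randomized and is unaffected.

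**5. What the limitations cover**

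The limitations paragraph of the Discussion concedes possible residual activity of the 10% granules (g) and response bias in the presence of concomitant psychological interventions. It does not say that the psychological component (P) drops out of the comparison.

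**The case against.** Efficacy is always relative to a comparator, and this one is disclosed openly in the Abstract, Trial Design, Blinding and Interventions sections. The regimen's definition specifies standard-dose granules, which is exactly the randomized feature. A shared background programme with matched granules is a legitimate add-on design that can be blinded, and it answers the granule question validly. The passage on the two components working together gives the rationale for combining them. No synergy endpoint or test is planned. All of this stands, and it limits the point to the objective and the permitted conclusion.

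A reader might go further and infer that a positive trial would say nothing about the regimen. The documents do not support that. If the shared programme and the 10% granules are not harmful, superiority over a partly active comparator understates the regimen effect, and the limitations paragraph already gives this direction for the granules. A reader might also choose a high control rate to make the gap look large. The only rate in the plan is 10%, which caps the gap at 10 points under the same assumption. Nor do the documents give the two components any weights, so no share of the regimen can be assigned to the psychological part.

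The objection does not remove the mismatch. The protocol names standard cancer treatment as the foundational therapy and writes the psychological programme into the experimental regimen. The objective names no comparator, and the limitations do not fill the gap.

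**Conclusion.** The point holds as a mismatch between the stated objective and the randomized contrast. The trial estimates the effect of full-dose against 10%-dose granules, each on top of the same psychological programme and standard care. It does not estimate the effect of the regimen as defined, the contribution of the psychological component, or joint action.

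A positive result is indirect and conservative evidence for the regimen, on the assumption that the shared programme and the low-dose granules are not harmful. A null result is not evidence that the regimen is ineffective. Under that assumption and the plan's 10% control rate, the difference between the two effects is between 0 and 10 percentage points. It could be larger if control remission turns out higher, since the bound equals the control rate.

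A reader might infer that the design is invalid or the sample size wrong. Neither follows: the design is sound for the granule question, and the 116 and 145 per group reproduce.

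**What to change.** Restate the primary objective and planned conclusion in the Abstract (Objective and Conclusions), the Objectives section and the opening of the Discussion, for example: to evaluate the effect of full-dose versus 10%-dose Compound Ciwujia Granules, each added to the same psychological intervention and standard care, on 3-month PNSC remission.

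Add to the limitations that the psychological component is common to both arms and cancels out of the contrast. The randomized comparison therefore does not support claims about the regimen as a whole or about synergy, and a null result should not be read as failure of the regimen.

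The cost is wording and a narrower headline claim. Conduct, analysis and sample size stay as they are. The Results section reports no recruitment as of April 2026, so the change can be made before any outcome data exist.
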